## **18.3 Data Sharing Statement**

Requests for data sharing will be reviewed on an individual basis by the CI.

The study will comply with the good practice principles for sharing individual participant data from publicly funded clinical trials [67] and data sharing will be undertaken in accordance with the required regulatory requirements and in the spirit of open research.

## 20 APPENDICES

|            |                                                      |
|------------|------------------------------------------------------|
| Appendix 1 | P/F Ratio Reference Table for Inclusion Criteria     |
| Appendix 2 | ARDSNet PEEP/FiO 2 Table                  |
| Appendix 3 | Guidelines for Management During Study Drug Infusion |

### Appendix 1: P/F Ratio Reference Table for Inclusion Criteria

| FiO2 | Maximum PaO2 if P/F ratio $\leq$ 27kPa |
|------|----------------------------------------|
| 0.50 | 10.0 kPa                               |
| 0.55 | 11.0 kPa                               |
| 0.60 | 12.0 kPa                               |
| 0.65 | 13.0 kPa                               |
| 0.70 | 14.0 kPa                               |
| 0.75 | 15.0 kPa                               |
| 0.80 | 16.0 kPa                               |
| 0.85 | 17.0 kPa                               |
| 0.90 | 18.0 kPa                               |
| 0.95 | 19.0 kPa                               |
| 1.00 | 20.0 kPa                               |

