## 8.3 Eligibility Criteria

Eligibility to participate in the trial will be confirmed by a medically qualified person who is named on the delegation log. The medical care given to, and medical decisions made on behalf of subjects, will be the responsibility of an appropriately qualified treating physician.

The P/F ratio table in appendix 1 can be used for reference. Patients will be eligible to participate in the study if they fulfil the following criteria:

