### Inclusion criteria

1. Moderate to severe ARDS as defined by the Berlin definition (62).
  - a) Onset within 1 week of identified insult
  - b) Within the same 24-hour time period
    - i. Hypoxic respiratory failure ( $\text{PaO}_2/\text{FiO}_2$  ratio  $\leq 27\text{kPa}$  on  $\text{PEEP} \geq 5\text{ cmH}_2\text{O}$ )
    - ii. Bilateral infiltrates on chest X-ray consistent with pulmonary oedema not explained by another pulmonary pathology
    - iii. Respiratory failure not fully explained by cardiac failure or fluid overloadThe time of onset of ARDS is when the last ARDS criterion is met.
2. Patient is receiving invasive mechanical ventilation.
3. COVID-19 based on clinical diagnosis or PCR test or other cause of ARDS.

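### Every row of the Appendix 1 eligibility table is computed at a P/F ratio of 20 kPa, although its header and inclusion criterion 1(b)(i) say 27 kPa

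*Protocol*

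**What the plan says.** Inclusion criterion 1 in Protocol section 8.3 asks for moderate to severe ARDS on the Berlin definition. Item (b)(i) makes this operational as a PaO2/FiO2 ratio of at most 27 kPa on PEEP of at least 5 cmH2O. Just before the criteria, section 8.3 tells sites: "The P/F ratio table in appendix 1 can be used for reference".

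Appendix 1 is that table. Its second column is headed "Maximum PaO2 if P/F ratio $\leq$ 27kPa". It has 11 rows, for FiO2 0.50 to 1.00 in steps of 0.05, and the PaO2 values rise by 1.0 kPa per row from 10.0 to 20.0 kPa. There are no rows below FiO2 0.50.

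The protocol nowhere states a P/F threshold of 20 kPa.

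**The concern.** The criterion and the table should give the same answer for the same blood gas, and they do not. The header carries the same threshold as the criterion, but the body of the table applies a lower one. The mistake is hard to see at the bedside because the header looks right.

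What is at stake is a single definition of eligibility. A site that divides PaO2 by FiO2 and compares the result with 27 kPa can enrol a patient whom a site reading the table would log as not meeting the oxygenation criterion. The reasons for non-enrolment in the screening log (section 8.2), which are meant to show how representative the recruited patients are, would then be wrong for some patients.

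**Working it through.** **Inputs.** The threshold of 27 kPa comes from section 8.3, criterion 1(b)(i), and the Appendix 1 header. The FiO2 and PaO2 pairs come from the Appendix 1 rows. The PaO2 target of 7 to 10 kPa comes from section 11.7, Mechanical Ventilation.

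**Step 1: limit at the stated threshold.** Maximum PaO2 = 27 × FiO2. The threshold that each printed row implies is printed PaO2 ÷ FiO2.

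| FiO2 | Printed limit (kPa) | Implied P/F (kPa) | 27 × FiO2 (kPa) | Shortfall (kPa) |
|---|---|---|---|---|
| 0.50 | 10.0 | 20.0 | 13.5 | 3.5 |
| 0.55 | 11.0 | 20.0 | 14.85 | 3.85 |
| 0.60 | 12.0 | 20.0 | 16.2 | 4.2 |
| 0.65 | 13.0 | 20.0 | 17.55 | 4.55 |
| 0.70 | 14.0 | 20.0 | 18.9 | 4.9 |
| 0.75 | 15.0 | 20.0 | 20.25 | 5.25 |
| 0.80 | 16.0 | 20.0 | 21.6 | 5.6 |
| 0.85 | 17.0 | 20.0 | 22.95 | 5.95 |
| 0.90 | 18.0 | 20.0 | 24.3 | 6.3 |
| 0.95 | 19.0 | 20.0 | 25.65 | 6.65 |
| 1.00 | 20.0 | 20.0 | 27.0 | 7.0 |

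The printed column cannot be reproduced at 27 kPa in any row. It is reproduced exactly at 20 kPa in all 11. The shortfall is 7 × FiO2, which is 7 ÷ 27 = 26% of the limit in every row. Rounding cannot produce gaps of 3.5 to 7.0 kPa. A series this regular is also not a fault of text extraction.

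**Step 2: a patient who gets two answers.** FiO2 0.60 with PaO2 14 kPa gives P/F = 14 ÷ 0.60 = 23.3 kPa. The criterion is met (23.3 ≤ 27). The table's limit at FiO2 0.60 is 12.0 kPa, so the table says no.

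**Step 3: where the printed rows mislead.** A row wrongly rejects when PaO2 lies above 20 × FiO2 and at or below 27 × FiO2. The lowest row is FiO2 0.50, so this needs PaO2 above 20 × 0.50 = 10 kPa. With PaO2 at or below 10 kPa and FiO2 at or above 0.50, P/F is at most 10 ÷ 0.50 = 20 kPa, and no printed row rejects the patient.

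**Step 4: the same band at PaO2 7 to 10 kPa.** FiO2 = PaO2 ÷ (P/F). The lowest value is 7 ÷ 27 = 0.26. The highest is just under 10 ÷ 20 = 0.50. The band therefore lies wholly at FiO2 below 0.50, where the table is silent. For example, FiO2 0.40 with PaO2 10 kPa gives P/F 25 kPa, which meets the criterion but has no row.

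**Step 5: direction.** Any patient the table passes has P/F at or below 20 kPa and so also satisfies the limit of 27 kPa. On the P/F threshold, the error only excludes.

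**The case against.** The table is optional. The criterion with its 27 kPa limit is written out in the same section, the header repeats it, and a medically qualified person confirms eligibility. During the trial the oxygenation target is SpO2 88 to 95% or PaO2 7 to 10 kPa, and at such PaO2 values no printed row rejects an eligible patient. All of this stands, and it limits the harm to staff who rely on the table. It does not remove the harm. The target governs care in the trial, and a screening gas may lie above it. Staff may also read a missing row as not eligible.

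Some stronger readings are tempting but are not supported:

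- **That the whole band from 20 to 27 kPa is lost.** Steps 3 and 4 show that the printed rows reject only part of it. For the rest, the table gives no answer.
- **That the trial population becomes sicker than moderate to severe.** Everyone the table passes meets the 27 kPa limit. At most, the enrolled patients are a more severe part of the intended population.
- **That recruitment slows, or that the day-7 OI mean and SD of 62 (51) in section 14.1 no longer apply.** The protocol gives no P/F distribution and does not give the entry criteria of the earlier trial behind those figures, so neither effect can be sized.
- **That the treatment comparison is biased.** Patients are randomised after eligibility is settled, with stratification by centre (section 10.2). Differences between sites in using the table affect who enters, not the comparison between arms.
- **That patients beyond 72 hours are admitted because onset is dated too late.** Onset is tied to the last ARDS criterion being met, but nothing says that the table is used to date it.

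**Conclusion.** The point holds as an internal contradiction that is exact in every row. Appendix 1 applies a P/F limit of 20 kPa under a header, and beside an inclusion criterion, that both say 27 kPa. Each printed limit is 26% below the one its header calls for.

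Staff who rely on the table may reject eligible patients with P/F above 20 and up to 27 kPa. Through the printed rows this happens only when PaO2 exceeds 10 kPa. The consequence is eligibility that can differ between sites, and possibly a more severe subset of the intended patients. How many patients are affected depends on how many have P/F in that band and how often sites use the table. The protocol gives neither figure, so no size is claimed.

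The conclusion rests only on the arithmetic of the table and on the threshold stated in the header and in section 8.3.

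**What to change.** Reconcile Appendix 1 with criterion 1(b)(i), so that the header, the rows and the criterion carry one threshold. If the 27 kPa criterion stands:

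- Reprint the PaO2 column for FiO2 0.50 to 1.00 as 13.5, 14.85, 16.2, 17.55, 18.9, 20.25, 21.6, 22.95, 24.3, 25.65 and 27.0 kPa.
- Add rows below FiO2 0.50, or state that the ratio must be calculated there.
- Notify sites of the correction.

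The cost is one corrected appendix page and a note to sites.

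Where screening logs exist, look for patients recorded as failing the oxygenation criterion with a worst P/F between 20 and 27 kPa. In phase 2 the log is kept only if possible and is anonymised (section 8.2), and eligibility lapses 72 hours after ARDS onset. The check can therefore gauge the impact but cannot recover patients.

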**Appendix 2: ARDSNet PEEP/FiO2 Table**

|             |     |     |     |     |     |     |     |     |
|-------------|-----|-----|-----|-----|-----|-----|-----|-----|
| FiO2 | 0.3 | 0.4 | 0.4 | 0.5 | 0.5 | 0.6 | 0.7 | 0.7 |
| PEEP | 5   | 5   | 8   | 8   | 10  | 10  | 10  | 12  |

|             |     |     |     |     |     |       |
|-------------|-----|-----|-----|-----|-----|-------|
| FiO2 | 0.7 | 0.8 | 0.9 | 0.9 | 0.9 | 1.0   |
| PEEP | 14  | 14  | 14  | 16  | 18  | 18-24 |

**Appendix 3: Guidelines for Management During Study Drug Infusion**

| Adverse Reactions                                                                                                                                                                                                                                          | Signs and Symptoms                                                                                                                                                                                                                                                                       | Management                                                                                                                                                                                                                                                                                                                                                                                                                                                                                                                                                                                                |
|-------------------------------------------------------------------------------------------------------------------------------------------------------------------------------------------------------------------------------------------------------------------|-------------------------------------------------------------------------------------------------------------------------------------------------------------------------------------------------------------------------------------------------------------------------------------------------|------------------------------------------------------------------------------------------------------------------------------------------------------------------------------------------------------------------------------------------------------------------------------------------------------------------------------------------------------------------------------------------------------------------------------------------------------------------------------------------------------------------------------------------------------------------------------------------------------------------|
| 
Hypersensitivity
 
Hypersensitivity to allogeneic plasma proteins.
                                                                                                                                                                             | 
 
• dyspnea
 
• hypotension
 
• fever
 
• urticaria
 
• tachycardia
 
• hypoxemia
 
                                                                                                                            | 
 
• Pause MSC infusion
 
• Check vital signs and O2 saturation
 
• Hydrocortisone IV 100-200 mg
 
• If severe adrenaline IV 1:10,000 50-100 microg (0.5-1ml).
 
• Increase supplemental O2 if O2 saturation is <93% and/or dyspnea
 
• Resume MSC infusion after reasonable resolution of signs and symptoms if considered safe to do so.
 
                                                                                                                                                 |
| 
Leukoagglutination
 
Because some leukocytes may be present in the MSC preparation (although MSC purity will typically be >95%), leukoagglutination symptoms may occur.
                                                                     | 
 
• cough
 
• “tickle in throat”
 
• dyspnea
 
• hypoxemia
 
• chest pressure
 
                                                                                                                                       | 
 
• Pause MSC infusion.
 
• Check vital signs and O2 saturation
 
• Increase supplemental O2 if O2 saturation is <93% and/or dyspnea.
 
• Resume MSC infusion after reasonable resolution of signs and symptoms.
 
                                                                                                                                                                                                                                                                                        |
| 
Reactions to Cryopreservatives (e.g. DMSO)
 
DMSO is added to all MSC products being cryopreserved to protect the MSC from hypothermal damage. The infusion of DMSO has side effects and consequences that study personnel need to be aware of
 | 
 
• metallic/garlic taste
 
• nausea/vomiting
 
• flushing of face
 
• intestinal cramps
 
• acute hypertension
 
• bradycardia (first, second, or third degree atrioventricular block on electrocardiogram)
 
 | 
 
• Pause MSC infusion.
 
• Check vital signs and O2 saturation.
 
• Administer additional anti-emetics if appropriate.
 
• If bradycardia, perform an electrocardiogram. If associated with hypotension, stop infusion and administer atropine 0.5-1mg.
 
• If bradycardia is present and ECG shows third degree atrio-ventricular block, consider placement of a temporary pacemaker. Consult Cardiology.
 
• Resume MSC infusion after reasonable resolution of signs and symptoms if considered safe to do so.
 
 |
